### Conceptual framework

The study adopts the transactional theory of stress and coping as its underpinning theoretical framework. Transactional theory proposes how people react to stress, and the intensity of the reaction is heavily influenced by the mediating role of appraisal, the cognitive process through which meaning is ascribed to events [32, 33]. By reordering life priorities based upon one’s values and goals and ascribing positive meaning to stressful events, meaning-focused coping helps to restore the resources that influence cognitive appraisals, sustain coping efforts over time and to provide relief from distress [34, 35].

Through continued mindfulness practice, we hypothesize that perinatal women can increase their maternal mindfulness. Increased maternal mindfulness can expand pregnant women’s perceptual awareness and facilitate positive appraisal during the stressful perinatal period, thereby helping to reduce perinatal psychological stress. This is consistent with the results of a previous study, where positive appraisal was found to be significantly increased in a mindfulness group [28]. Moreover, by reducing perinatal psychological stress, the increase of maternal mindfulness is theorized to lead to higher HRV, suggesting increased parasympathetic control. A decrease in perinatal psychological stress can bring about better birth outcomes (obstetric and neonatal) through increased parasympathetic activity. Fig 1 depicts this conceptual model.

**Fig 1 pone.0270683.g001:**
[figure not shown]
Conceptual framework.

### Four hypotheses

The intervention group would show a greater increase in maternal mindfulness and positive appraisal than the control group at T1, T2 and T3.The intervention group would show a greater reduction in stress and depression than the control group at T1, T2 and T3 and these outcomes would be mediated by the enhancement in positive appraisal.The intervention group would show a greater increase in HRV than the control group at T1, T2 and T3 and these outcomes would be mediated by the reduction in stress and depression.The levels of stress and depression would be negatively associated with obstetric and neonatal outcomes at T3 and these correlations would be mediated by HRV.

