**Primary outcome variables**		
Maternal psychological stress		
General stress	Perceived Stress Scale –10 items–The scale measures subjective perception of stress with two subscales, perceived helplessness and perceived self-efficacy [36, 37].	T0, T1, T2, T3,
Pregnancy- specific stress	Prenatal Distress Questionnaire– 12 items–The scale consists of three factors–concerns about birth and baby, weight and body image, emotions and relationships [38].	T0, T1, T2
Depression	Edinburgh Postnatal Depression Scale–Chinese– 10 items–The scale has been validated in the Chinese population with satisfactory psychometric properties [39].	T0, T1, T2, T3
Mindfulness		
State mindfulness	Short-form Five Facet Mindfulness Questionnaire– 20 items–The scale consists of five subscales–observing, describing, acting awareness, non-judging of inner experience and non-reacting to inner experience [40].	T0, T1, T2, T3
Daily mindfulness	Daily Mindful Responding Scale– 4 items–A measure designed to assess mindful responding in the daily lives of people undergoing mindfulness training [41].	Every week until T3
Positive appraisal		
Coping	Prenatal Coping Inventory– 22 items–consists of four subscales–preparation, avoidance, positive appraisal and prayer [42].	T0, T1, T2
Heart rate variability		
HRV Index	CorSense by Elite HRV–A merchandise device monitoring heart rate variability	T0, T1, T2, T3

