### Data analysis

Quantitative data including scale measures and the HRV index will be collected at four time-points as articulated above.

Intention-to-treat analysis will be performed and missing data due to drop–out will be handled by the ‘multiple imputation’ technique [51]. 1) Using a two-arm RCT design, the efficacy of the intervention will be examined by repeated measures MANOVA on both the primary and secondary outcome variables, while adjusting for individual factors. Partial eta-squared values will be calculated to measure the effect size; values of .02, .13 and .26 suggest small, medium, and large effect sizes, respectively [52]. 2) To investigate the within-group effect, serial trend analysis from T0 to T3 will be conducted on the primary and secondary outcome variables. 3) A series of linear mixed-effects models will be fitted to assess the mediation effects. 4) The software Elite HRV Team Dashboard will be used for HRV data collection. Three HRV indexes will be computed for analysis, namely RMSSD (Mean squared difference between consecutive normal-to-normal intervals), SDNN (standard deviation of beat-to-beat intervals) and HF (absolute power of HF band).

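### Positive appraisal and pregnancy-specific stress are not measured at T3, so the T3 appraisal hypothesis and any T0–T3 analysis of these two primary scales cannot be done

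*Protocol article*

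**What the plan says.** Under Four hypotheses, the first reads: "The intervention group would show a greater increase in maternal mindfulness and positive appraisal than the control group at T1, T2 and T3". The second reads in part: "greater reduction in stress and depression than the control group at T1, T2 and T3 and these outcomes would be mediated by the enhancement". The mediator it goes on to name is positive appraisal.

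Table 1 lists the primary outcomes with their visits. Positive appraisal is one of four subscales of the Prenatal Coping Inventory ("preparation, avoidance, positive appraisal and prayer"), scheduled at T0, T1 and T2. Pregnancy-specific stress is measured by the Prenatal Distress Questionnaire ("concerns about birth and baby, weight and body image, emotions and relationships"), also at T0, T1 and T2. The Perceived Stress Scale and the Edinburgh Postnatal Depression Scale (EPDS) are scheduled at all four visits. The Daily Mindful Responding Scale is weekly until T3.

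The Data analysis section opens by saying that the scale measures and HRV are collected at four time-points. It then plans that "the efficacy of the intervention will be examined by repeated measures MANOVA on both the primary and secondary outcome variables", adjusted for individual factors. A within-group trend analysis from T0 to T3 covers the same outcomes. Multiple imputation is planned for data missing through drop-out. In Table 1 the individual factors are socio-demographic items and social support. The baseline value of the outcome is not among them.

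**The concern.** Three parts of the article cannot all stand: the hypotheses, the measurement table and the analysis section. Positive appraisal is a primary outcome and also the mediator on which the conceptual framework turns. If the text is left as it is, the analyst must decide after the data are in whether to drop T3, drop the instruments or redefine the mediator.

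A second, smaller matter sits in the same analysis sentence. Repeated measures MANOVA over visits that include T0 treats the baseline as a response, although treatment cannot affect it. The adjustment set does not bring the T0 value in as a covariate. Information that is already collected is then used inefficiently.

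**Working it through.** **1. Schedule against claims**

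| Primary scale | Table 1 visits | What is claimed or planned at T3 | Possible? |
|---|---|---|---|
| Prenatal Coping Inventory (appraisal) | T0, T1, T2 | Hypothesis 1 contrast; T0–T3 trend | No |
| Prenatal Distress Questionnaire | T0, T1, T2 | T0–T3 trend; not named in hypothesis 2 | No |
| Perceived Stress Scale | T0–T3 | Hypothesis 2 contrast | Yes |
| EPDS | T0–T3 | Hypothesis 2 contrast | Yes |

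For hypothesis 2 at T3, the outcome exists but the mediator at the same visit does not. Appraisal at T1 or T2 is available as an earlier mediator. The text does not say that it will be used.

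**2. The plan's own figure**

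The Sample size section gives 99 per arm for effect size 0.4, 90% power, p < .008 and 25% attrition. These inputs alone do not determine 99. A plain two-sided comparison with d = 0.4 needs 2(2.652 + 1.282)²/0.4² = 193.4, so 194 per arm, or 194/0.75 = 259 with attrition. Repeated-measures formulas reach a total of 198 only at particular correlations that are not stated. The figure is neither confirmed nor refuted, and the schedule contradiction does not depend on it. It is used here only for the number of completers: 99 × 0.75 = 74.25, so n = 74 per arm.

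**3. T0 as response or as covariate**

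Assumptions not in the article: 0.4 is Cohen's d, covariance is compound symmetric, and the correlation ρ is .3, .5 or .7. Alpha is .008. Let δ be the arm differences at T1–T3 in SD units, with n/2 = 37.

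- *Joint group-by-time test, T0 as response.* λ = 37[Σδ² − (Σδ)²/4]/(1 − ρ), F on 3 and 144 df.
- *Joint test at T1–T3, T0 as covariate.* λ = 37[Σδ² − ρ(Σδ)²/(1 + 3ρ)]/(1 − ρ), F on 3 and 143 df.
- *Average of T1–T3, T0 as covariate.* λ = 37(mean δ)²/[(1 + 2ρ)/3 − ρ²], F on 1 and 145 df.

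Sustained effect, δ = (0.4, 0.4, 0.4), so Σδ² = 0.48 and Σδ = 1.2:

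- T0 as response: λ = 4.44/(1 − ρ) = 6.34, 8.88, 14.80.
- T0 as covariate, joint or average: λ = 17.76/[(1 − ρ)(1 + 3ρ)] = 13.35, 14.21, 19.10.

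Fading effect, δ = (0.4, 0.2, 0), so Σδ² = 0.20 and Σδ = 0.6:

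- T0 as response: λ = 4.07/(1 − ρ) = 5.81, 8.14, 13.57.
- T0 as covariate, joint: λ = 7.57, 9.47, 14.64.
- Average: λ = 1.48/(.443, .417, .310) = 3.34, 3.55, 4.77.

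Power at ρ = .3/.5/.7:

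| Effect at T1, T2, T3 | Joint, T0 as response | Joint, T0 as covariate | Average, T0 as covariate |
|---|---|---|---|
| 0.4, 0.4, 0.4 | 27/42/73% | 67/71/87% | 83/86/95% |
| 0.4, 0.4, 0 | 40/59/88% | 58/71/92% | 40/43/59% |
| 0.4, 0.2, 0 | 24/38/68% | 34/46/72% | 20/22/31% |

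The joint test with T0 as covariate is ahead of the joint test with T0 as response in every row. The average is ahead only when the effect lasts.

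**4. The two scales without T3**

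A T0–T2 analysis is feasible. For a sustained 0.4 effect, the 2-df group-by-time test with T0 as response has 28/43/73% power. The baseline-adjusted average of T1 and T2 has 71/77/91%.

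**The case against.** The strongest reply is that little here is impossible. It stands on several counts:

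- **Hypothesis 2.** It speaks of stress without naming the pregnancy-specific scale, and both general stress and depression are measured at T3. A reader might infer that its T3 part is untestable. It is not, and mediation need not be concurrent.
- **The MANOVA.** A reader might infer that it cannot be run at all for the two prenatal scales. The article attaches the T0–T3 span to the trend analysis, and a T0–T2 version of the MANOVA is possible.
- **Imputation.** Nothing suggests that an unscheduled T3 would be imputed, because imputation is confined to drop-out.
- **Daily mindfulness.** The starting week of the weekly scale is not given, so its lack of a baseline is not established.

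On power, one might conclude that the planned test is simply wasteful and that a baseline-adjusted average should replace it. The documents do not support that. The deciding MANOVA effect is not stated, and neither is any correlation. The hypotheses predict an effect at each visit but not an equal one. The Introduction reports that earlier mindfulness studies found no significant postnatal benefit in stress and depression over control. If the effect has gone by T3, the average only matches or falls below the planned joint test. Repeated measures with T0 as a response is also a valid analysis, not an error.

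This reply does not remove the T3 contradiction. It also does not answer the narrower point about baseline adjustment. If the group main effect over T0–T3 were decisive instead, T0 would dilute it: λ = 37 × 0.3²/[(1 + 3ρ)/4], giving 49/36/27% for a sustained effect.

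**Conclusion.** The schedule contradiction is established from the text and needs no assumption. The T3 part of hypothesis 1 for appraisal cannot be tested, no T0–T3 analysis of the two prenatal scales can be done, and appraisal at T3 cannot serve as a concurrent mediator. The remaining T3 contrasts in hypothesis 2 are sound.

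Using T0 as a covariate is a recommended improvement of conditional size. At ρ = .5 the joint test gains 29 percentage points for a sustained effect (42% to 71%) and 8 for a fading one (38% to 46%). These figures rest on reading 0.4 as Cohen's d, on compound symmetry, on 74 completers per arm and on the assumed correlations. Which contrast should decide is a trade-off for the investigators.

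**What to change.** 1. Limit the claims and analyses for positive appraisal and pregnancy-specific stress to T1 and T2.
2. State that appraisal at T1/T2 is the mediator for stress and depression at T3.
3. Correct the statements about four time-points and the T0–T3 trend so that they follow each scale's schedule in Table 1.
4. Analyse each primary outcome at its own .008 level in a model whose responses are its scheduled post-baseline visits, with its T0 value as covariate where collected. Linear mixed models are already planned for mediation.
5. Fix in advance whether the joint test, the visit-specific differences or the average over visits decides. The average favours a lasting effect and loses power for a fading one.

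No new data are needed. The first three items change wording only. The last two give up a single multivariate omnibus p-value, and because they change the deciding test, the sample size statement should be checked against the one chosen.

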### Randomization and allocation

The participants’ recruitment will proceed on a continual basis so once begun, a random allocation process will be performed weekly. Online interview will be conducted to ensure eligibility. We use computer-based random number generator to assign numbers to the eligible participants. The research assistant will toss the coin to decide the group allocation and ensure allocation concealment. Two research assistants will interview the participants to check eligibility and obtaining consent. One of the two research assistants will assign random number to the participants, and allocate participants to intervention or control group.

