**Method:**

This study is a randomized controlled trial that follows a parallel design. Consenting pregnant women in their second trimester (between 12^th^ and 20^th^ week gestation) will be randomly assigned to an intervention group (GMBPMI) or a control group (psychoeducation). The intended sample size is 198, with 99 participants in each group. Three levels of outcomes will be measured at baseline, post intervention in both the intervention and control groups, and at 36-week gestation and five-week postpartum. The primary outcomes include maternal psychological stress, mindfulness and positive appraisal HRV. Secondary outcomes are psychological and physical wellbeing. Tertiary outcomes include obstetric and neonatal outcomes, and social support. Analyses will follow an intention-to-treat method and repeated measures MANOVA will be conducted to compare changes in primary and secondary outcomes. A series of mixed-effects models will be fitted to assess the mediation effects.

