### Sample size calculation

The previous eastern-based meditation intervention (EBMI) study reported an effect size of 0.44 in reducing prenatal distress and an attrition rate of around 20% [28]. In the proposed study we assume an overall moderate effect size of 0.4 and a conservative attrition rate of 25%. Setting a power at 90%, a significance level of *p* < .008 (corrected for six primary outcomes), a sample size of 99 per arm is needed for a two-arm repeated measures design (GPower, version 3.1). Thus, the targeted total sample size is 198. Considering this is a web-based intervention, we will consider expanding the sample size to ensure enough statistical power after preliminary data analysis.

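### Allocation concealment is credited to a coin toss, but the allocator is one of the two assistants who screen and take consent, so concealment is claimed and not secured

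*Protocol article*

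**What the plan says.** All of the following is in the protocol article, mostly under Randomization and allocation.

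- Timing: recruitment is continual and "a random allocation process will be performed weekly".
- First mechanism: "We use computer-based random number generator to assign numbers to the eligible participants".
- Second mechanism: "The research assistant will toss the coin to decide the group allocation and ensure allocation concealment".
- Who screens and takes consent: "Two research assistants will interview the participants to check eligibility and obtaining consent".
- Who allocates: "One of the two research assistants will assign random number to the participants, and allocate participants to intervention or control group".
- Intended split (Abstract, Method): "The intended sample size is 198, with 99 participants in each group". The Sample size calculation section gives the same numbers.
- Blinding section: participants cannot be blinded to their group, though the study purpose is masked from them. The statistician is blinded. Nothing is said about the assistants.

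**The concern.** Concealment protects a trial only if whoever enrols a participant can neither know nor influence the arm she gets. Here the stated division of roles joins enrolment and allocation in one person, and the device said to guarantee concealment is a toss that this person could repeat or set aside.

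The stake is selection bias. The article's Introduction reports that in an earlier trial of a mindfulness intervention the benefits appeared only in the 56% who practised regularly, and that lack of continued motivation was the commonest reason for stopping. An interviewer can form a view of motivation before the arm is settled. If more motivated women ended up in the mindfulness arm, the comparison would favour the intervention whatever its true effect. The Data analysis section adjusts for individual factors, but Table 1 lists these as socio-demographic data and social support. Motivation is not among them.

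**Working it through.** **1. Who does what.** Eligibility and consent lie with two assistants. The random number and the allocation lie with one of those two. The tosser is called only the research assistant and is not expressly identified as one of the pair, but the allocator is. The overlap between enrolling and allocating is therefore stated, not inferred.

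**2. Which mechanism decides the arm.** Three readings fit parts of the text:

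- The number is a label and each woman's arm is a toss.
- The numbers order a weekly batch and the toss decides which set gets which arm.
- The number decides the arm and the coin adds nothing, which conflicts with the sentence on the coin.

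The section does not choose between them. Under all three the allocator has been part of screening and consent, so the concealment problem does not depend on the reading. The arm sizes do.

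**3. Order of steps.** Numbers go to women already found eligible. The Abstract describes consenting women as being assigned, which suggests that consent comes first, but the Randomization section does not fix that order. The Design section calls T0 pre-intervention, which is not the same as pre-allocation. Fig 2 could not be seen and may say more.

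**4. Possible size of selection bias (assumption, not an estimate).** Let p be the share of allocations that are steered, and δ the difference in mean outcome, in SD units, between steered women in the two arms. Then bias = p × δ.

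| | p = 0.05 | p = 0.20 |
|---|---|---|
| δ = 0.5 | 0.025 SD | 0.10 SD |
| δ = 1 | 0.05 SD | 0.20 SD |

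The plan assumes an effect of 0.4 and does not name the metric. Read as a standardised mean difference, the bias would be 6% (0.025/0.4) to 50% (0.20/0.4) of it. No input to p or δ comes from the document.

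**5. The planned 99 per arm.** Inputs from Sample size calculation: effect 0.4, 90% power, significance level .008, 25% attrition. A plain two-sided two-sample formula gives 2 × (2.652 + 1.282)² / 0.4² ≈ 194 per arm before attrition, not 99. A repeated-measures calculation can reach 99. For example, Cohen's f = 0.2 (a standardised difference of 0.4), a group-by-time interaction with two measurements and a correlation of about 0.25 gives 148 in total, and 74/0.75 ≈ 99 per arm. The correlation, the number of measurements and the effect metric are not stated, so 99 can be neither confirmed nor refuted. It is taken as given, and the point does not rest on it.

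**6. Arm sizes under one fair toss per woman.** The size of one arm is Binomial(198, 0.5).

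- P(exactly 99:99) = 5.7%.
- SD of one arm = √(198 × 0.25) = 7.04. SD of the difference between arms = √198 = 14.07.
- Central 95% range: 85 to 113 per arm.
- P(89:109 or more unequal) = 17.7%.

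**7. Power cost of that imbalance.** Relative efficiency is 4·n₁·n₂/198². Anchored at the stated 90% for 99:99, power = Φ(3.934 × √efficiency − 2.652).

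| Split | Efficiency | Power |
|---|---|---|
| 99:99 | 1.000 | 90.0% |
| 89:109 | 0.990 | 89.6% |
| 85:113 | 0.980 | 89.3% |

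**The case against.** Concealment means that the recruiter cannot foresee the next arm when deciding whether to enrol. A fair toss made after enrolment cannot be foreseen, and the section gives numbers only to women already found eligible. This stands. A reader might infer that concealment is absent altogether, or that assistants would steer women without meaning to. The text does not support either: steering past a fair toss needs a deliberate re-toss or override. What remains is that nothing in the stated procedure prevents one.

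A reader might also infer that no record of allocations is kept. The article is silent on logging, which a condensed article may leave to the full protocol, so that is not claimed here. The joining of roles is different: it is stated, and a fuller document would have to contradict it to cure it.

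A third tempting reading is that coin tossing defeats the planned 99 per arm. The article gives 99:99 as an intention, the probabilities above assume one independent toss per woman, and a toss over numbered weekly sets could give near balance. Even under individual tosses the power cost is negligible.

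The plan has some protections: a masked study purpose, baseline measurement of the main scales, adjustment for individual factors and one device-measured primary outcome (HRV). They help, but none replaces concealed allocation. The self-report of unblinded women is a separate source of bias that concealment would not prevent, so it does not enlarge this point.

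**Conclusion.** The concern holds in this form: the concealment claim is not supported by the procedure described, because a screening and consenting assistant also allocates, and the random number and the coin are not reconciled. Concealment is not secured; the document does not show that it is absent. The size of any selection bias cannot be derived from the document. The 6% to 50% illustration rests wholly on assumed values of p and δ and on reading 0.4 as a standardised mean difference. Selection on unmeasured characteristics could not be repaired in the analysis, and this is what gives the point its weight. Unequal arm sizes are secondary: less than one point of power across the central 95% range, if every woman has her own fair toss.

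**What to change.** Rewrite the Randomization and allocation section so that one mechanism decides the arm and no recruiter controls it:

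- Remove the coin toss.
- Before recruitment, have an existing team member who neither recruits nor analyses, or an automated tool, generate one 1:1 list in permuted blocks of randomly varying size.
- Hold the list in a locked electronic system that the recruiting assistants cannot view.
- Release each arm, with a time stamp, only after eligibility, consent and T0 data are logged. The weekly rhythm can stay.
- Give the statistician coded arms only. The statistician should not generate the list, because whoever writes it knows the key, and the Blinding section keeps the statistician blind.

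Blocking also keeps the arms near 99:99, a minor gain. If any women have already been allocated, report how this was done and in which role.

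The cost is a small effort to set up the list and its release system, one rewritten paragraph, and the amendment application to the ethics committee that the Trial status section already foresees.
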